#### Secondary outcome measures analysis

The secondary outcome measures (FM-UE, BBT, PANU, BI, and actimetry) will be used to assess the changes in UL impairment, function, non-use, and ADL from V1 at inclusion to V2, and V2 to V3.

#### Other/exploratory outcome measures analysis

The outcome measures from the 3 functional motor tasks (Seated reaching, circular steering task, Armeo ladybug game) will be used to assess changes in UL performance (e.g., targets reached, IP, speed, accuracy, performance variability) and bihemispheric motor cortical regional activation (e.g., fNIRS-LI and EEG-ERD) from V1 to V2, and V2 to V3. Linear mixed models for the evolution of all these measures will be derived to assess the effect of time (V1, V2, V3) and of group (intervention, placebo). The interaction of group with time will be tested, along with the interaction of group with changes between V1 and V2 and between V2 and V3.

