#### Randomization

The Capture System software (Ennov Clinical, module randomization, Paris, France) will be set up by the randomization administrator, from the Innovation and Research Department of the Hospital, to give a blinding code to each patient. A centralized randomization will be performed using the Capture System software (Ennov Clinical, module randomization, Paris, France). A minimization algorithm will assure the balance of groups regarding PRM centres (CHU Montpellier or Nimes) and stroke severity (FM-UE score lower or higher than 40 [72]); see “Blinding of group and stimulation protocols” section for more details. For each inclusion, another hospital department, the clinical investigation centre, will use the software to allocate the right protocol.

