### Description of testing visits and outcome measures

Table 2 presents the timing of the testing visits and outcome assessment measures. The baseline assessment (pre-test) visit (V1) will take place on the first day of the 3-week in-patient hospital rehabilitation stay. A specialist trained therapist will run the clinical assessments (WMFT, FM-UE, Box and Block Test (BBT), Bell’s test, MMSE, Barthel Index (BI); more details in the “Clinical data and outcome measures” section). Patients UL kinematics and motor cortical region activation will then be evaluated by one of the investigators on three functional motor tasks: a seated reaching task (Proximal Arm Non-Use, PANU), a circular steering task, and the Ladybug game of the Armeo VRT platform used for rehabilitation. The next day (day 2), patients will start the standard in-patient stroke rehabilitation program that will last for 13 complete days (excluding weekends) over 3 weeks.

**Table 2 Tab2:** Study testing visits (V1-3) and outcome assessments

Outcome measures	Inclusion visit	Pre-test (V1)	Post-test (V2)	Retention test (V3, 3 months after V2)
Mini Mental State Examination	X			
Boston diagnostic aphasia examination	X			
Bell’s test	X			
Wolf Motor Function Test		X	X	X
Fugl-Meyer Upper Extremity		X	X	X
Box and Block Test		X	X	X
Barthel Index		X	X	X
Actimetry		X	X	X
Proximal Arm Non-Use (PANU)^a^		X	X	X
Reaching task (Kinematics and EEG/fNIRS)		X	X	X
Circular steering task (Kinematics and EEG/fNIRS)		X	X	X
Lady bug test (Kinematics and EEG/fNIRS)		X	X	X

^a^Proximal Arm Non-Use will be assessed during the reaching task

*EEG* Electroencephalography, *fNIRS* Functional near-infrared spectroscopy

The post-test visit (V2) will take place the last day of the 3 weeks (day 19); the post-test will be identical to the pre-test. The 3-month visit (V3) will take place 3 months after the end of the rehabilitation program (day 19) for a retention test and will be identical to the pre- (V1) and post- (V2) tests.

Patients will be given actimetry bracelets to be worn on each UL to measure UL activity for 7 days before V1, for 7 days after V2, and for 7 days after V3.

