#### Statistical method

Statistical analysis will be performed using the latest version of the free R software. A *p*-value of 0.05 will be considered significant for all analyses. All outcome measures will be assessed at V1, V2, and V3. The primary outcome will be the difference between both groups (*intervention, placebo*) at V3 on the WMFT. The secondary outcomes will be the changes between V1 and V2 (learning) and between V2 and V3 (retention) for both groups.

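### Exploratory mixed models treat the pre-treatment visit V1 as an outcome with no stated baseline adjustment, which costs precision in the V1-to-V2 contrast

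*Protocol article*

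**What the plan says.** In the protocol article, the section Other/exploratory outcome measures analysis covers the three functional motor tasks and the fNIRS and EEG measures. It states: "Linear mixed models for the evolution of all these measures will be derived" and gives their purpose as "to assess the effect of time (V1, V2, V3) and of group". It continues: "The interaction of group with time will be tested, along with the interaction of group with changes between V1 and V2 and between V2 and" (the quotation stops one word short, before the last visit is named). V1 is therefore a level of the response. The section states neither a common V1 mean in the two arms nor V1 as a covariate, and it gives no factor coding.

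Two other places fix the status of V1. Description of testing visits and outcome measures says "The baseline assessment (pre-test) visit (V1) will take place on the first day" of the in-patient stay, with the rehabilitation programme starting the next day. Randomization says "A minimization algorithm will assure the balance of groups regarding PRM centres" and FM-UE class.

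The primary analysis lies outside this model. Under Statistical method, "The primary outcome will be the difference between both groups" at V3 on the WMFT. Secondary outcome measures analysis describes changes "from V1 at inclusion to V2, and V2 to V3" but names no model.

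**The concern.** V1 is measured before the first stimulation session in randomised, blinded groups. Any group difference seen there is chance. A model that gives each arm its own V1 mean spends information on estimating a quantity whose expected value is known to be zero.

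This has two consequences:

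- The group-by-(V1 to V2) interaction, which is the learning comparison, becomes a difference in raw change scores. It is valid, but less precise than a contrast that constrains or adjusts for V1. The trial plans on only 26 analysable patients per arm, so the loss can be noticeable when visits are moderately correlated.
- The section lists an effect of group among the things to be assessed. If that is taken as an average over V1, V2 and V3, it mixes a visit with no treatment effect into two visits that may have one. If V1 is the reference level in a model with interaction, the group coefficient is only the baseline difference. Neither quantity is the treatment effect.

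**Working it through.** **The plan's own figure.** Sample size gives d = 0.8, two-sided alpha 5%, power 80%, 26 per group and 58 in total. The normal approximation gives 2 × (1.960 + 0.842)² / 0.8² = 24.5, so 25. The exact t-test needs 26 (power 80.7%). Allowing for 10% loss, 26 / 0.9 = 28.9, so 29 per group and 58 in total. The figure reproduces. It belongs to the WMFT comparison; the article states no figure for the mixed models.

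**Inputs for the check.** n = 26 per arm (Sample size). SD is set to 1 at each visit. The true group difference is 0 at V1 and d at V2 and V3. The correlation rho is an assumption. d = 0.8 is borrowed from the WMFT for illustration only. Visits are taken as compound symmetric, with AR(1) as a check.

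**V1-to-V2 contrast.**

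- V1 free in each arm: variance = (2/n) × 2(1 − rho).
- V1 constrained equal, or adjusted for: variance = (2/n) × (1 − rho²).
- Ratio = 2(1 − rho) / [(1 − rho)(1 + rho)] = 2/(1 + rho).

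Example at rho = 0.5: 4 × 0.5 / 26 = 0.0769 against 2 × 0.75 / 26 = 0.0577, a ratio of 1.33. Power is approximately Φ(d/SE − 1.96).

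| rho | variance ratio | power at d = 0.8, V1 free | power at d = 0.8, V1 constrained |
|---|---|---|---|
| 0.3 | 1.54 | 68% | 86% |
| 0.5 | 1.33 | 82% | 92% |
| 0.7 | 1.18 | 96% | 98% |
| 0.8 | 1.11 | 99.5% | 99.8% |
| 0.9 | 1.05 | above 99% | above 99% |

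The noncentral t (50 df, noncentrality d/SE) gives slightly lower values, for example 95.5% against 97.7% at rho = 0.7. With an assumed d = 0.6 it gives 56% against 69% at rho = 0.5, 78% against 84% at 0.7, and 92% against 94% at 0.8. The V1-to-V2 ratio is the same under AR(1), because those visits are adjacent.

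**V2-to-V3 contrast.** V1 helps only through its covariance with the change Y3 − Y2. Under compound symmetry that is rho − rho = 0, so the ratio is 1.00. Under AR(1) it is rho² − rho, and the ratio is 2 / [2 − rho²(1 − rho)]: 1.03, 1.07, 1.08, 1.07 and 1.04 at rho = 0.3, 0.5, 0.7, 0.8 and 0.9.

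**Group effect over the three visits.** With equal weights its expected value is (0 + d + d)/3 = 2d/3, which is 0.533 when d = 0.8. In a fit without interaction, V1 takes 33% of the weight under compound symmetry and 37% to 48% under AR(1). With V1 as reference level and interaction terms present, the group coefficient has expected value 0.

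**The case against.** A longitudinal model with V1 as a response and group-by-time tests is valid and common. The interactions named in the section match the declared questions of learning (V1 to V2) and retention (V2 to V3), and under randomisation they are unbiased and undiluted. That stands: preferring a constrained baseline is a choice about efficiency, not the repair of a biased analysis. At rho of 0.8 or more the gain is small.

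A reader might infer more in four ways, and the article supports none of them.

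- *That the plan's treatment effect is biased towards zero.* The article never names the group main effect as the efficacy estimate, and the interactions sit beside it. The two-thirds figure applies only if someone averages over the visits and reports the result as efficacy. Setting the power of that average (about 58% at d = 0.8 and rho = 0.7) against a baseline-adjusted V2/V3 average (above 99%) compares the best alternative with a test that the plan does not name for efficacy.
- *That both change contrasts waste the baseline.* The V2-to-V3 contrast does so barely or not at all.
- *That the secondary outcomes share the defect.* Their section uses the same change intervals but names no model.
- *That centre and FM-UE class are left out of the model.* The article is silent on covariates, and a condensed article may leave them to the analysis plan. A baseline constraint could also be set there. The case for stating it here is that the section already spells out the model's terms and contrasts.

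**Conclusion.** The point holds as a precision matter confined to the other/exploratory outcomes. As written, the V1-to-V2 group contrast is an unadjusted change-score comparison, with 11% to 54% more variance than necessary for rho from 0.8 down to 0.3, and 5% more at 0.9. The V2-to-V3 contrast loses between nothing and about 8%. No bias is shown in either contrast. An overall group effect across V1 to V3 would not be a treatment effect under either coding considered, so the article should rule out reading it that way.

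The variance ratios rest on equal SDs, complete data and assumed correlations. The power figures also rest on an effect size that the article justifies only for the WMFT. The free group effect at V1 is the natural reading of the text, not an explicit statement. The primary WMFT comparison and N = 58 do not depend on any of this.

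**What to change.** In Other/exploratory outcome measures analysis, state that:

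- the longitudinal model has a common V1 mean in both arms, or uses V1 as a covariate with V2 and V3 as outcomes;
- the between-group differences at V2 and at V3 are reported with confidence intervals, and the declared V2-to-V3 retention contrast is kept. If a gain is fully kept, that contrast is expected to be zero, so the V3 difference is a needed companion to it;
- the overall group main effect across V1 to V3 is not interpreted as efficacy.

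The cost is a sentence or two of analysis wording. It needs no new data, visits or patients, and the sample size does not change.

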### Ethic and reglementary aspect

The research will be conducted in compliance with the French regulations in force, in particular the provisions relating to research involving humans: Law No. 2012-300 of 5 March 2012 relating to research involving humans and its implementing decrees (decree No. 2016-1537 of November 16, 2016, relating to research involving humans, decree No. 2017-884 of May 9, 2017, amending certain regulatory provisions relating to research involving humans), the laws of Bioethics (if applicable), Law No. 78-17 of January 6, 1978, as amended, relating to computing, files and freedoms, the Declaration of Helsinki, and good clinical practices. In the context of this research involving the category 2 human person, the authorization of the competent authority is not required. For information, the sponsor sends the favourable opinion of the CPP and the summary of the protocol to the competent authority.

Prior to carrying out this research involving the human person, the subject’s free, informed consent will be obtained after being informed, by the investigator during a consultation and after a sufficient period of reflection. The information intended for trial participants include all the elements defined in Law No. 2012-300 of 5 March 2012 relating to research involving the human person (Jardé Law) and is written in a simple manner, in language understandable by the participant.

The Montpellier University Hospital, sponsor of the study, has taken out a civil liability insurance contract for the entire duration of the study with Newline Syndicate 1218 at Lloyd’s guaranteeing its own civil liability as well as that of any party involved in the conduct of the trial, regardless of the nature of the links between the participants and the sponsor.

The data recorded during this research are subject to computer processing under the responsibility of the Montpellier University Hospital, the sponsor, in compliance with the law no. 78-17 of January 6, 1978, as amended relating to the IT, files, and freedoms.

## Discussion

The aim of the ReArm project is to evaluate the additional effects on paretic UL function by including anodal HD-tDCS during a 3-week intensive VRT program to supplement conventional therapy in late subacute and chronic stroke patients.

VRT and conventional therapy are equally effective in improving paretic UL function in stroke patients [45]; however, VRT is less labour intensive from a physiotherapy and occupational therapy perspective for the same clinical gains. So therapists can focus on other aspects of rehabilitation as such as providing encouragement, directions, and observing the quality of movement. As such, the PRM departments of Montpellier and Nimes University Hospitals have integrated VRT sessions into conventional therapy sessions as a standard in-patient stroke rehabilitation program. Anodal HD-tDCS is as a relatively simple and easily applied NIBS technique that has been shown to enhance motor cortical excitability and plasticity. Anodal HD-tDCS is an ideal candidate to help boost re-learning of paretic UL function in chronic stroke patients. Accordingly, combining anodal HD-tDCS with VRT rehabilitation could further improve neuroplastic effects induced by VRT alone and lead to greater and sustainable clinical gains [11].

The quadruple-blind, randomized, sham-controlled, bi-centre, two-arm parallel, interventional design of the ReArm project was implemented to ascertain whether adding anodal HD-tDCS, a more focalized and intensive form of anodal tDCS, during 3 weeks of VRT (13 × 30-min sessions) that complements conventional therapy (39 × 30-min sessions) would lead to greater and sustained improvements in paretic UL function. We are expecting a significantly improved functional recovery of the paretic UL for the group receiving real anodal HD-tDCS (*n* = 29) compared to the group receiving sham stimulation (*n* = 29). We will evaluate the effects of the ReArm rehabilitation program using various paretic UL assessments of (i) motor function (WMFT, FM-UE), (ii) prehension dexterity (BBT), (iii) non-use (PANU), (iv) everyday life activities (BI), and (v) motor performance (IP, speed, accuracy, compensation, variability). We will also determine pain, fatigue, and perceived exertion after each VRT session as well as neural biomarkers of paretic UL function by assessments of ipsilesional and contralesional motor cortical region plasticity (fNIRS-LI, amplitude, time to peak and EEG-alpha and beta ERD) during functional motor tasks. Although the primary outcome is based on the clinical assessment of the WMFT at 3 months after the intervention, the ReArm project’s multiple secondary and exploratory outcome measures allows to probe other aspects of paretic UL recovery that may benefit from the boost to neuroplasticity afforded by anodal HD-tDCS supplemented during the VRT sessions, which include novel assessments of paretic UL non-use (PANU), use-in ADL (actimetry), and performance (speed and accuracy), including a mechanistic understanding of such paretic UL improvements through neuroplasticity changes in ipsilesional motor cortical regional activation monitored using non-invasive and portable neuroimaging technologies (fNIRS and EEG).

With support from our primary and secondary outcome results, the impact of the ReArm project for the public health care system could be a better efficiency of paretic UL rehabilitation for chronic stroke patients at unchanged or lower cost. With combined HD-tDCS and VRT, we expect a better paretic UL recovery without an increased rehabilitation time commitment, without an increased human resource costs (e.g., physiotherapy and occupational therapy time) but with a relatively minor hardware related costs (tDCS device and consumables) costs. Moreover, this innovative treatment with HD-tDCS is adapted to a majority of patients, since tDCS allows to stimulate the patient while receiving rehabilitation treatment. Therefore, tDCS has a promising clinical potential in post-stroke rehabilitation [61, 63]. Thus, improving the efficiency of recovery for a majority of stroke patients may have an impact on patients’ health and on public health costs.

The benefit for the patients taking part of this study could be a better efficiency of the rehabilitation without changing the length of the rehabilitation programs. Indeed, the association of the two methods proposed (anodal HD-tDCS and VRT) could allow, for the same dose of rehabilitation, a better and faster recovery of the paretic UL function. Patients could thus enter in the virtual spiral of “use it and improve it” aided by the rehabilitation efficiency [38]. This could lead the patient to a better independence on daily life activities and to a better life quality.

### Dissemination plan

The results derived from the primary and secondary outcome analysis of this project will be reported in peer-reviewed journal articles and presented at leading national and international conferences. Results derived from the other/exploratory outcome analysis of only the baseline (V1) session will be included in the PhD thesis of CM. Results will be communicated to health professionals and participants through meetings and email/letter, respectively.

## Abbreviations

ADL: Activities of daily life
BI: Barthel Index
BBT: Box and Block test
EEG: Electroencephalography
FM-UE: Fugl-Meyer Upper Extremity
fNIRS: Functional near-infrared spectroscopy
HD-tDCS: High-definition transcranial direct current stimulation
NIBS: Non-invasive brain stimulation
PANU: Proximal Arm Non-Use
UL: Upper limb
VRT: Virtual reality therapy
WMFT: Wolf Motor Function Test
